#### Participant timeline {13}

Additional file is attached.

### Sample size {14}

#### Qualitative stage

Considering the fact that qualitative studies seek rich data and the greatest diversity, participants will not select solely from those who refer to the Diabetes Clinic of Shahid Mohammadi Hospital in Bandar Abbas (Bandar Abbas Diabetes Center). Sampling will be carried out using a maximum variation of the purposive sample (in terms of age, educational status, marital status, employment status, diabetes status, and adherence to treatment status). Sampling will continue without any limit on the number of samples until reaching the saturation stage. We will use the information from the medical files registered with the Diabetes Clinic of Shahid Mohammadi Hospital in Bandar Abbas to identify eligible patients

#### Intervention stage

When designing the educational intervention, the two intervention and control groups will be selected from T2D patients with registered medical cases in the Diabetes Clinic of Shahid Mohammadi Hospital in Bandar Abbas. According to previous study [19], the pooled standard deviation is calculated to be 29.7. Also, assuming a type I error = 5%, test power = 80%, and also considering a 13.5-score difference in adherence to treatment of the intervention and control group, the sample size of each group is estimated to be equal to 76 [20]. Considering the 10% possible drop-out, the sample size is determined 83 people in each of the two groups.$$n=\frac{2{\left({z}_{1-\frac{a}{2}}^2+{z}_{1-\beta}\right)}^2{s}_p^2}{{\left({\mu}_1-{\mu}_2\right)}^2}=76$$

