**Methods:**

This mixed method study will consist of qualitative stage, questionnaire design and a randomized, open-label, parallel-group interventional study based on HPM in southern Iran. Sampling for qualitative stage will continue until reaching the saturation. In the intervention stage, participants will be 166 T2D patients referring to the Bandar Abbas Diabetes Clinic will be randomized into intervention and control groups (allocation 1:1). After identifying the factors affecting adherence to treatment in T2D patients by qualitative study and literature review, a questionnaire based on HPM will be designed. In the next stage, 10 sessions of intervention for the intervention group will be designed. To evaluate the effect of the intervention, intervention and control groups will be tested for hemoglobin A1c (HbA1c) before and 3 months after the intervention.

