### Trial design {8}

This mixed-method study consists of 3 phases.

Need assessment as the first step aims to identify the factors affecting adherence to treatment in T2D patients. Different qualitative and quantitative data sources will be used for need assessment. After combining the results of the need assessment, a questionnaire based on HPM to measure adherence to medication, physical activity, and diet will be designed. In the next stage, based on earlier phases the intervention will be designed. The intervention phase with a superiority design is a randomized, open-label, parallel-group study. The participants will be randomly assigned at a 1:1 ratio to control and intervention groups. The intervention group will participate in an intervention program to improve T2D treatment adherence treatment (medication, diet, and physical activity) based on the Pender health promotion model. To evaluate the effect of the intervention, intervention and control groups will be tested for hemoglobin A1c (HbA1c) before and after the intervention.

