#### Questionnaire design

The research team will categorize the results of the need assessment according to the constructs of HPM. Then, based on these categorized results, a treatment adherence questionnaire in accordance with HPM will design for T2D patients.

The questionnaire will be consisting of two parts: The first part is the demographic profile, which includes age, marriage, type of diabetes medication, age at the onset of diabetes, co-morbidities, and type of insurance covered. The second part will be based on constructs of HPM to measure adherence to medication, physical activity, and diet: perceived benefits of behavior, perceived barriers to behavior, perceived self-efficacy, activity-related affect, interpersonal and situational influences, immediate competing demands and preferences, commitment to plan of action, and health promotion behaviors.

The questionnaire, will be investigated and approved in terms of qualitative and quantitative content validity, face validity, construct validity through confirmatory factor analysis (CFA), and internal and external reliability.

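### The 76 per group is reproducible, but its formula is misprinted, 83 per group falls slightly short of covering 10% drop-out, and the SD and difference are not tied to the questionnaire to be used

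*Protocol article*

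**What the plan says.** All the figures stand in the Protocol article, Sample size {14}, Intervention stage:

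- SD: "According to previous study [19], the pooled standard deviation is calculated to be 29.7".
- Difference: "considering a 13.5-score difference in adherence to treatment of the intervention and control group". No source is attached to this value.
- Error rates: "assuming a type I error = 5" per cent, with 80% power. The formula takes the normal quantile at 1 − a/2, so the test is two-sided.
- Result before drop-out: "the sample size of each group is estimated to be equal to 76".
- Result after drop-out: "Considering the 10% possible drop-out, the sample size is determined 83 people in each of the two groups". The abstract carries the same total: "participants will be 166 T2D patients".

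The displayed formula puts an exponent of 2 on the alpha quantile inside a bracket that is itself squared, and ends in 76.

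Trial design {8} fixes the allocation: "The participants will be randomly assigned at a 1:1 ratio to control and intervention groups". Outcomes {12} names treatment adherence as the primary outcome, measured by the score of a questionnaire that the researchers will build and by HbA1c. Questionnaire design describes that instrument as future work: "a treatment adherence questionnaire in accordance with HPM will design for T2D patients". Its validity and reliability are also still to be examined.

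**The concern.** A sample-size paragraph should let a reader go from inputs to result, and should deliver its stated power under its stated loss. Here a reader who applies the formula as printed does not arrive at 76, and one who applies the stated drop-out does not arrive at 83.

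The third matter has the most substance. Power for a difference in points depends on the SD of the score in which those points are counted. The planning SD cannot have been estimated on the trial's questionnaire, because that questionnaire did not yet exist. The protocol gives neither a range nor an expected SD for the new score. The statement that the trial has 80% power for 13.5 points therefore cannot be checked for the score that will be analysed.

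**Working it through.** **Inputs** (Sample size {14} and Trial design {8}): SD 29.7; difference 13.5; two-sided 5%, z = 1.95996; power 80%, z = 0.84162; allocation 1:1; drop-out 10%.

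**1. The plan's own 76.** Standard formula: n = 2 (z₁₋α/₂ + z₁₋β)² SD² / difference².

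- SD²/difference² = 882.09 / 182.25 = 4.84
- (1.95996 + 0.84162)² = 2.80158² = 7.849
- n = 2 × 7.849 × 4.84 = 75.98, so **76 per group**

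This matches the protocol. An exact t-based calculation gives 77, a difference of no consequence.

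**2. The formula as printed.** With the alpha quantile squared inside the bracket:

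- 1.95996² + 0.84162 = 3.8415 + 0.8416 = 4.6831
- n = 2 × 4.6831² × 4.84 = 212.3, rounded up to 213

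The printed expression therefore does not equal the 76 beside it. Removing the inner exponent restores agreement.

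**3. Drop-out.**

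- To retain 76 after 10% loss: 76 / 0.9 = 84.4, so 85 per group (170 in total)
- Adding 10%: 76 × 1.1 = 83.6, so 84 when rounded up; the stated 83 is consistent with rounding down
- With 83 enrolled and 10% lost: 83 × 0.9 = 74.7 per group
- Largest loss that leaves 76: 1 − 76/83 = 8.4%

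Power for an unadjusted comparison of means, at SD 29.7 and difference 13.5:

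| Analysed per group | Normal approximation | t-based |
|---|---|---|
| 74 | 79.0% | 78.4% |
| 74.7 | 79.3% | 78.8% |
| 75 | 79.5% | 79.0% |
| 76 | 80.0% | 79.5% |
| 83 (no loss) | 83.4% | 82.9% |

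**4. The scale.** The one quantity free of units is the standardised difference, 13.5 / 29.7 = 0.4545, or about 0.45. The 76 per group is the size for 0.45 SD on any scale. It is the size for 13.5 points only if the new score's SD is 29.7.

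With 74.7 per group analysed, the difference detectable at 80% power is 2.80158 × √(2/74.7) = 0.458 SD. In points, that is 0.458 times whatever SD the new score proves to have.

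**The case against.** **The size is sound and the exponent is a slip.** This stands. The line with the stray exponent ends in 76, so the exponent was not used in the calculation, and every input is also given in words. A reader might infer from 213 against 76 that the trial is undersized nearly threefold, or that 76 does not follow from its inputs. Neither is supported: 213 is only what the misprint yields.

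**The drop-out gap is trivial.** Largely true. It is two patients per group and about one point of power, and the 10% is itself described only as possible. Statistical methods {20a} also lists analysis of covariance. The documents give no correlation between baseline and follow-up. Under the usual variance factor 1 − r², with r assumed at 0.2, 0.3 and 0.5, power with 74.7 per group would be about 81%, 83% and 89%; r of about 0.13 already restores 80%. The shortfall therefore applies to an unadjusted comparison, which is what the formula describes. The arithmetic of 83 remains short of its stated purpose.

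**Borrowing an SD is ordinary practice, and the instrument of the cited study is not visible.** Also fair. A reader might infer that both the SD and the 13.5 points belong to another questionnaire. The protocol attributes only the SD to the earlier study, so for the 13.5 one can say only that it has no stated source and is not tied to the new score.

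**Any large loss of power is hypothetical.** True. Holding 13.5 points and 76 per group fixed, assumed SDs of 20, 25, 35 and 40 give about 99%, 91%, 66% and 55% power. A reader might take this as the trial's actual exposure. It is not: those SDs have no basis in the documents, and on a different scale the worthwhile difference in points would normally change too. At 0.45 SD the requirement stays at 76. The range shows only why the SD of the new score must be known before power is quoted in points.

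**Conclusion.** The point holds in a limited form.

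- **Formula:** printed wrongly; the calculated 76 is correct, so this is an editorial correction.
- **Drop-out:** 83 per group is below both 84 and 85. After 10% loss, unadjusted power is about 79% (79.3% normal, 78.8% t-based). By the normal approximation, 80% holds only up to 8.4% loss. This rests on the protocol's SD and difference, and adjustment for baseline may offset it.
- **Scale:** the 80% power for 13.5 points is not established on the trial's own score, because the SD predates the questionnaire and the difference has no stated source. How far the true power differs cannot be said from the documents. This part rests on the inference that an SD from an earlier study cannot have been measured on an instrument still to be designed.

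None of this shows that more patients are required.

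**What to change.** In Sample size {14}, Intervention stage:

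1. Remove the exponent from the alpha quantile, so that the sum of the two quantiles is squared once.
2. State that 83 per group gives about 79% unadjusted power after 10% loss, and 80% for losses up to 8.4%.
3. Express the target as a standardised difference of about 0.45, and give the source or rationale for 13.5 points.
4. When the validation sample yields the SD of the new score, restate before the first randomisation the point difference the trial can detect: about 0.46 times that SD with 10% loss.

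Step 4 fits the planned order of work. Trial design {8} places the questionnaire before the intervention, and Recruitment {15} expects intervention recruitment in November 2022, after a needs assessment begun in February 2022.

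The cost is wording and one recalculation, with no extra patients. The downside is a slightly less favourable stated power.

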#### Recruitment {15}

The first author arranges appointments to explain the study process to the patients and requests them to complete the informed consent form if they are eligible. Needs assessment as the first stage started in February 2022, and the expected recruitment of patients referred to Diabetes Clinic of Shahid Mohammadi Hospital in Bandar Abbas for intervention will be in November 2022. The study is anticipated to continue until March 2023.

### Assignment of interventions: allocation

#### Sequence generation {16a}

Randomization will be done through systematic random sampling by a biostatistics expert according to the list of participants (whose eligibility has been confirmed and registered in the diabetes clinic). Then, selected participants will randomly be assigned in a 1:1 ratio to the control group or intervention group.

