#### Implementation {16c}

After obtaining signed informed consent forms, the first author will generate the allocation sequence, enroll, and assign participants to interventions.

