#### Methods for additional analyses (e.g., subgroup analyses) {20b}

A subgroup analyses will be performed for insulin to oral anti-diabetic drugs administrations.

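### The section on sequence generation labels list sampling as randomisation and names no assignment mechanism, and drug treatment, the only planned subgroup factor, is used in neither allocation nor the stated analysis

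*Protocol article*

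**What the plan says.** All references are to the protocol article.

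- **Sequence generation {16a}** has two sentences. One states that "Randomization will be done through systematic random sampling by a biostatistics expert according to the list of participants", the list being of eligible patients registered at the clinic. The next says that "selected participants will randomly be assigned in a 1:1 ratio to the control group or intervention group". The ratio is given; the tool that produces the random assignment is not.
- **Implementation {16c}** says that, once consent is signed, "the first author will generate the allocation sequence, enroll, and assign participants to interventions". The section on sequence generation gives the randomisation to the biostatistics expert instead.
- **Trial design {8}** repeats the ratio: "The participants will be randomly assigned at a 1:1 ratio to control and intervention groups". **Sample size {14}**, intervention stage, sets the target: "the sample size is determined 83 people in each of the two groups".
- **Methods for additional analyses {20b}** plans one subgroup factor: "A subgroup analyses will be performed for insulin to oral anti-diabetic drugs administrations".
- **Questionnaire design** lists type of diabetes medication among the items of the first part, and **Intervention description {11a}** has a pre-test with that questionnaire.
- **Statistical methods {20a}** names t-tests and analysis of covariance, without covariates.

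**The concern.** Systematic sampling means taking every k-th name after a random start. With 1500 registered patients and 166 needed, that is a sensible way to decide whom to approach. Placed under sequence generation and called randomisation, it becomes the only named mechanism in the section that should describe how arms are formed. Someone implementing the section has a precise method for selection and none for allocation.

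The second matter is drug treatment. The authors think it important enough to be their single planned subgroup factor, and they collect it. If it also predicts the adherence score, chance imbalance in insulin use adds noise to the main comparison. Stratifying on a baseline value that is already collected, and adjusting for it, would remove that noise. At stake are clarity of the allocation procedure and a small amount of precision.

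**Working it through.** **1. The plan's own figure.** Inputs from Sample size {14}: SD 29.7, difference 13.5, and "assuming a type I error = 5%, test power = 80"%; two-sided, as the formula's 1 − α/2 implies.

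n = 2 × (1.960 + 0.842)² × 29.7² / 13.5² = 75.98, so 76 per group, as stated. With 10% added, 76 × 1.1 = 83.6, against 83 stated. The target of 83 per arm (166 in all) is taken as given below.

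**2. Would unequal arms matter?** Power for arms of size a and b is Φ(13.5 / (29.7 × √(1/a + 1/b)) − 1.96).

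- 83/83: standard error 29.7 × √(2/83) = 4.61; power 83.4%.
- If each of 166 patients were assigned by an independent coin toss, 83/83 would occur in 6.2% of trials, and the 95% range for one arm would be 70 to 96.
- 70/96: power 82.4%. Average over all coin-toss splits: 83.1%.
- After 10% loss in each arm: 79.3% at 83/83 and 78.3% at 70/96.

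So even unrestricted assignment would cost about 1 point of power at the edge of the 95% range and about 0.2 points on average.

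**3. Imbalance in insulin use.** The document gives no insulin share, so 20% to 50% is assumed. With 83/83 fixed and m insulin users among 166, the number k in one arm is hypergeometric, and the difference in insulin share is |2k − m| / 83.

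| Assumed share | m | P(difference ≥ 10 points), 83/83 fixed | Same, coin toss |
|---|---|---|---|
| 20% | 33 | 11.9% | 10.4% |
| 30% | 50 | 12.7% | 16.2% |
| 40% | 66 | 15.3% | 19.4% |
| 50% | 83 | 21.4% | 18.8% |

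The SD of the difference is 2 × √(p(1 − p)/165), which is 6.2 points at m = 33 and 7.8 points at m = 83. Forcing equal arms therefore does not remove this imbalance; stratification does.

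**4. Effect on the main comparison.** Assume insulin and oral users differ by 15 points on the score (not in the document). A 10-point imbalance gives 0.10 × 15 = 1.5 points. That is 1.5 / 13.5 = 11% of the design difference and 1.5 / 4.61 = about one third of a standard error.

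**5. Gain from adjusting.** Under the same assumption, drug type explains p(1 − p) × 15² of the variance: 36 at 20% and 56.25 at 50%. Against 29.7² = 882, that is 4.1% to 6.4%. The standard error falls by a factor of √(1 − 0.041) = 0.979 to √(1 − 0.064) = 0.968, which is 2% to 3%.

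**6. The subgroup analysis.** With 33 to 83 insulin users, power to detect 13.5 points among them is 26% to 54% with an even split and 25% to 53% at 60:40. Its limit is size, not balance.

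**The case against.** The strongest reply is that the two sentences, read together, already give the right order: sample from the list, then assign at random 1:1. On that reading only a label is loose. This largely stands. A reader might infer that list position determines the arm; that requires ignoring the second sentence, and the document does not support it.

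A reader might also infer that assignment is unrestricted, so that 83/83 is left to luck. The document does not say so. It fixes the ratio and 83 per group, and a random split of a known list of 166 gives exactly 83/83 without blocks. The 6.2% in step 2 is conditional on a method that the article never states. Block details may sit in the full protocol, which is not shown, and their absence is no fault here.

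Finally, stratification is optional. Without it the comparison remains unbiased, chance imbalance is already part of the standard error, a planned subgroup does not require a stratified design, and adjustment for the baseline score in the analysis of covariance could absorb part of any imbalance. All of this stands, and it limits the point to an inexpensive improvement.

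What the reply leaves untouched is that the section names a selection method as the randomisation, gives no mechanism for the assignment, and disagrees with Implementation {16c} on who generates the sequence.

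**Conclusion.** The point holds as a modest one. The wording under sequence generation needs correcting because it calls selection randomisation and leaves the assignment mechanism unnamed. Separately, the one factor singled out for subgroup analysis is used in neither allocation nor the stated model.

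No systematic bias follows. Unequal arms are not shown to be a risk and would hardly matter. The statistical stake is a 12% to 21% chance of a 10-point insulin imbalance with 83/83 fixed. An imbalance of exactly 10 points is worth about 1.5 points against a standard error of 4.6, and adjustment would narrow that standard error by some 2% to 3%. These figures rest on two assumptions without a source in the document: 20% to 50% of patients on insulin, and a 15-point gap between drug groups. A smaller gap shrinks the effect in proportion. The disagreement over who generates the sequence is plain from the text and needs no assumption.

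**What to change.** - **Sequence generation {16a}:** say that systematic sampling serves only to choose whom to invite. State that allocation is by a computer-generated random sequence giving 83 per arm, stratified by drug treatment (any insulin versus oral drugs only) as recorded at the pre-test, before allocation.
- **Statistical methods {20a}:** include that stratum as a factor in the analysis of covariance.
- **Implementation {16c}:** reconcile with the section on sequence generation, so that both name the same role as generating the sequence.

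The cost is protocol wording and a short program, with no extra patients. The one practical demand is that drug type be recorded before assignment; the article shows that the questionnaire collects it, but not that it is known for every patient on the list. The gain in precision is modest, and the subgroup analysis will remain underpowered.

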#### Concealment mechanism {16b}

Details of the allocation process will be concealed. The randomizer and first and second authors are informed of the randomization result.

#### Implementation {16c}

After obtaining signed informed consent forms, the first author will generate the allocation sequence, enroll, and assign participants to interventions.

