#### Who will take informed consent? {26a}

The first author will enroll participants, will explain the purpose and process of intervention, and will obtain informed consent in both qualitative and intervention stages.

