#### Intervention description {11a}

The intervention will be designed based on HPM constructs for T2D patients. The emphasis of the intervention materials will be on predictors of behavior that have been identified based on the need assessment and a pre-test that will be performed using the researcher-made questionnaire. The first author will recruit participants, will explain the purpose and process of intervention, and will obtain their informed consent to participate. According to the intervention program, the participants will not receive any other relevant education or training during the intervention. Sessions will present by one health education and promotion specialist and one internal specialist medicine, experienced in T2D treatment adherence. Intervention including 10 educational sessions in groups of 15 to 20 patients will be a combination of online and face-to-face methods according to the intervention group conditions. The intervention will be using challenging lectures, educational video clips, posters and pamphlets, and the main content of the sessions will be to promote and improve adherence to treatment in the areas of medication, diet, and physical activity. In-person sessions will be set to an average of 45 min and online sessions to 15 min. The control group will receive training at the end of the study.

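### The protocol conflicts on who generates the allocation sequence, and as Implementation {16c} is written the person who recruits and enrols also makes it, so the claimed concealment is not secured

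*Protocol article*

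**What the plan says.** Three adjoining sections of the protocol article describe allocation.

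- Sequence generation {16a} places the task with the statistical member of the team: "Randomization will be done through systematic random sampling by a biostatistics expert according to the list of participants". It then describes a second step, in which those selected are allocated at random 1:1, and does not name who carries this out.
- Concealment mechanism {16b} asserts that the allocation details are kept hidden and goes on to list who is told the outcome: "The randomizer and first and second authors are informed of the randomization result". It does not say how concealment is achieved or when the result is passed on.
- Implementation {16c} places the task elsewhere: "After obtaining signed informed consent forms, the first author will generate the allocation sequence, enroll, and assign participants to interventions".

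Other sections give the first author the contact with patients before allocation. The section on consent, {26a}, puts it this way: "The first author will enroll participants, will explain the purpose and process of intervention, and will obtain informed consent". Intervention description {11a} likewise makes the first author responsible for recruiting and for consent. Recruitment {15} adds that this same person sets up the appointments at which the study is explained and consent is sought. Who will be blinded {17a} makes clear that no one, including the biostatistics expert, is blinded.

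**The concern.** Concealment of allocation has to work against one person above all: whoever decides which patient is approached, consented and entered next. It is separate from blinding and can be kept in an open-label trial. If the person who enrols also makes the sequence, or can see it before enrolment is complete, patients can be entered, delayed or passed over according to the arm they would receive.

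That matters in this trial. The intervention aims to change adherence, and a patient's motivation to adhere lies close to the outcome. A recruiter who thought the programme worthwhile could favour motivated patients for it without any intent to mislead. HbA1c is part of the primary outcome and is objective, but that guards against biased measurement and not against arms that differ from the start. The analysis of covariance in {20a} can adjust for measured baseline values. It cannot be relied on for a trait that is not recorded. An allocation fault of this kind cannot be repaired after enrolment.

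**Working it through.** The plan gives no figure on this point, so the check is a comparison of sections.

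**1. Who generates the sequence?**
- {16a}, whose subject is sequence generation, gives randomisation to the biostatistics expert.
- {16b} names a randomizer and, separately, the first and second authors. The randomizer is thus someone other than the first author.
- {16c} gives generation to the first author.

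{16a} and {16b} fit together; {16c} fits neither. {16a} can be read as giving the expert only the drawing of the sample, because its 1:1 step names nobody. That does not remove the conflict: the text stands under the sequence heading, calls the act randomisation, and {16b} still has a separate randomizer. It would also leave the first author as the only named generator, which is the weaker arrangement for concealment.

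**2. Which tasks fall to the same person under {16c}?**
- Recruiting: first author ({11a}, {15}).
- Taking consent: first author ({26a}, {11a}).
- Enrolling: first author ({26a}, {16c}).
- Generating the sequence: first author ({16c}).
- Assigning: first author ({16c}).
- Holding the sequence apart from the enroller: nobody named.

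**3. In what order?** {16c} puts generation after signed consent, but lists enrolling and assigning after generating. Two procedures fit the text:
- *Whole list.* All patients consent and are irrevocably entered, and one list is then randomised. Nobody can foresee an allocation at enrolment. What remains is that an unblinded recruiter who makes the list could redraw it unchecked.
- *Patient by patient.* A sequence is made once consents begin to arrive, and enrolment continues against it. The enroller then knows the next allocation.

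The document does not choose between them.

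**4. Does {16b} settle it?** It asserts concealment but names no mechanism, no holder and no time at which the two authors learn the result. Under {16c} one of those authors already has the sequence.

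**5. Can the bias be sized?** Suppose patients are of two kinds whose mean outcomes differ by δ, and steering raises the share of the better kind by q in one arm and lowers it by q in the other. The difference between arms with no treatment effect is then 2qδ. The document gives neither q nor δ, so any number would only restate an assumption.

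**The case against.** The strongest reply is that {16c} places generation after consent. A sequence that does not yet exist cannot guide whom the recruiter approaches. {16a} works from a list, {15} expects recruitment in a single month (November 2022), and sessions are given to 15 to 20 patients at a time. All of this is compatible with allocating a complete list at once. This stands in part. A reader might infer that there is no concealment at all, or that the recruiter will foresee each allocation; the text does not show either. What it shows is that concealment is claimed without the order or custody that would secure it.

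Other inferences also go further than the document:

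- *That systematic sampling is the allocation method, applied to the clinic list.* {16a} can be read as two steps, sampling and then 1:1 assignment of those selected, and that order is compatible with assignment after consent. The wording is loose and needs clarifying, but it is not a proven error of method.
- *That the first author judges eligibility.* No section says who does. {15} requests consent from eligible patients, and {16a} treats eligibility as already confirmed. Discretion over whom to approach remains possible.
- *That knowing the randomisation result is itself a breach.* In an open-label trial the study team must learn it at some point. The gap in {16b} is the missing statement of when.
- *That self-report is the problem.* The questionnaire is only one part of the primary outcome, and self-report bears on measurement, not on selection.
- *That a bias of a given number of points follows.* The inputs to such a figure would have to be invented.

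**Conclusion.** The point holds in a limited form. {16a} and {16c} conflict on who generates the sequence, and {16b} sides with {16a} by naming a separate randomizer. If {16c} is followed, the unblinded person who recruits, consents and enrols also generates the sequence and assigns, with no separate custody and no fixed order between completing enrolment and generation. The concealment stated in {16b} is then not secured, and selection bias is possible. Whether it would occur, and how large it would be, cannot be determined from the document.

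The conflict and the missing separation of roles rest on the wording of the sections alone. How serious the risk is depends on whether allocation is done once for a closed list (small) or patient by patient (larger), which is left open. It should be corrected before enrolment: this is a stated rule that undermines the protocol's own claim, and analysis cannot repair the consequence.

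**What to change.** - **{16a} and {16c}:** only the biostatistics expert generates and holds the computer-generated 1:1 sequence. Remove sequence generation from the first author's tasks.
- **{16c}, order of steps:** the first author completes consent, enrolment, the baseline questionnaire and baseline HbA1c; the expert then releases the allocation. Release for the whole enrolled list at once is preferable, because nothing can then be foreseen. If release is patient by patient, use simple randomisation or blocks of varying, undisclosed size. Blocks of a guessable size would let an unblinded recruiter predict the later allocations in each block.
- **{16b}:** state that the first and second authors learn an allocation only after that patient's enrolment and baseline are complete.
- **{16a}:** make clear that systematic sampling only selects whom to invite and plays no part in assigning arms.

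The cost is protocol wording and some messages between existing team members; Study setting {9} already lists a biostatistics expert on the research team. The protocol is version 1 of 17 March 2022 and expects intervention recruitment in November 2022, so on its own timetable the change can be made before any patient is allocated.
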